#### **6.5 Description and justification of route of administration and dosage**

Not applicable.

#### **6.6 Dosages, dosage modifications and method of administration**

Not applicable.

#### **6.7 Preparation and labelling of Investigational Medicinal Product**

Not applicable.

#### **6.8 Drug accountability**

Not applicable.

## **7. NON-INVESTIGATIONAL PRODUCT/TREATMENT**

### **7.1 Name and description of non-investigational product(s)**

Not applicable.

### **7.2 Summary of findings from non-clinical studies**

Not applicable.

### **7.3 Summary of findings from clinical studies**

Not applicable.

### **7.4 Summary of known and potential risks and benefits**

Not applicable.

### **7.5 Description and justification of route of administration and dosage**

Not applicable.

### **7.6 Dosages, dosage modifications and method of administration**

Not applicable.

### **7.7 Preparation and labelling of Non Investigational Medicinal Product**

Not applicable.

### **7.8 Drug accountability**

Not applicable.

Fout! Bladwijzer niet gedefinieerd.

## 8. METHODS

### 8.1 Study parameters/endpoints

#### 8.1.1 Main study parameter/endpoint

- Long-term scar quality 12 months after skin transplantation assessed with the Patient and Observer Scar Assessment Scale (POSAS).

#### 8.1.2 Secondary study parameters/endpoints (if applicable)

- Long-term scar quality 3 and 12 months after skin transplantation
  - Subjective measurement of scar quality with Patient and Observer Scar Assessment Scale (POSAS). This is based on multiple aspects of scar formation such as: vascularization, pigmentation, texture, thickness, pliability, itch and pain, and is performed by member of research team and by patient.
  - Objective measurements of scar color and pigmentation with the Mexameter or Dermaspectrometer. Skin elasticity is objectively measured with the Cutometer.
- Skin graft technique preferred by patient
  - Patient gives overall indication as to what skin graft technique he/she would prefer if he/she were to require skin grafting again: weekly during admission, and at 3 and 12 months follow up
- Donorsite size and ratio of donorsite size and actual graft size (cm^2)
  - Surface areas will be calculated with a 3D-camera (Woundworks inSight)
- Take rate of skin grafts
  - Take rate will be clinically assessed at 8 +/- 2 days and expressed as the percentage of micrografted and meshed graft take
- Healing time
  - Clinical assessment of wound healing 14 and 21 days +/- 2 post application expressed as percentage of the total wound surface area healed
  - Time to complete wound closure where complete wound closure is defined as > 95% re-epithelialization of the wound with the absence of drainage and no longer needing a substantial wound dressing
- Bacterial load
  - Wound swabs for semi-quantitative investigation
  - Semi-quantitative bacteriology in both groups
  - Percentage of patients within both groups with clinical wound infection requiring systemic antimicrobial therapy
  - 'Clinical infection' is defined as the presence of cellulitis and/or visible purulence and/or lymphangitis combined with one or more of the following: local wound pain/erythema/edema/malodor

- Pain
  - Will be evaluated in the autografted target wounds with help of a Visual Analogue Scale (VAS score) on day 2 post surgery, before and after removal of Surfasoft®/Urgotul in case of meshed skin grafts or plissees in case of micrografting, and thereafter once weekly during the hospitalization period. After hospital discharge pain will be evaluated again at the 3 and 12 months follow ups
- Number of secondary procedures
  - Re-interventions in study areas due to insufficient take or necessity of reconstructive surgery
- Mobility at 3 and 12 months
  - If articulations of limbs are involved the Quick Dash for upper extremities and the Lower extremity functional scale for lower extremities, the range of motion will be assessed with a goniometer
- Quality of life
  - Assessed at the time of hospital discharge and at 3 and 12 months after the procedure. 3 quality of life measures, the EQ5D-5L, SF36 and DLQI will be used at different points in time: at the time of hospital discharge and 3 and 12 months post wound healing
- Health economics
  - Differences in operation time, costs of materials/equipment used and staff/personnel and impact of re-interventions and the need for reconstructive surgery will be evaluated. Using regression analysis based on the processing of the EQ5D-5L, SF36 and the DLQI we will be able to construct an economic model. The model will incorporate the short-term costs involved of both skin expansion techniques as well as the long-term costs.
- Incidence of AE and SAE
  - There are no Adverse Events (AEs) expected, relating to this study (comparison of two already practiced skin grafting techniques).
  - A Serious Adverse Event (SAE) is any untoward medical occurrence in a subject who is participating in a clinical study performed. This is defined as an event that is:
    - a) fatal
    - b) life-threatening
    - c) requires or prolongs inpatient (unexpected) hospitalization
  - These SAEs will be reported directly to the METc.
  - SAEs related to surgical treatment in general will be noted in a line-listing and will be reported yearly to the METc. These are defined as an event that results in a:
    - a) pneumonia
    - b) urinary tract infections
    - c) sepsis

- d) pulmonary embolism
- e) re-operation

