### 3. STUDY DESIGN

This study is a multicenter randomized intra-patient controlled trial conducted in the burn centers of the Red Cross Hospital Beverwijk in the Netherlands and of the University Hospital Ghent in Belgium. Inclusion period is three years. Individual patient follow-up is 12 months.

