### **Skin grafting techniques**

#### Micrografting

First debridement of the (burn) wounds to be grafted is performed according to local protocol, until a vital wound bed shows. Hemostasis is secured. The surface area of the to be grafted wounds is estimated by the amount of cork squares (42x42 mm) that matches the total wound bed. Thereafter, split thickness skin graft (SSG) of 0.1mm is harvested with the Zimmer dermatome from the in advance selected donorsite area. After harvesting, an alginate wound dressing with adrenaline suspension is placed on the donorsite and the SSG is placed with the dermal site on cork square and cut off. This procedure is repeated until the whole SSG is divided over cork squares, including all small graft fragments. Next, the cork fragments are placed in a holder and passed through the cutting machine. The SSG is cut in 14 long stripes of 3 mm wide. The cork square is now rotated for 90° and passed through the cutting machine again, the graft is now subdivided in little 196 squares of 3x3 mm. Now adhesive spray is applied on the epidermal (upper) site of the graft. When the graft is dried, the cork square is pressed on a double layered pre-folded gauze (plissee). Subsequently, the cork square is removed, which leaves all graft squares on the plissee. Expansion is obtained by traction on all four sides of the plissee, expansion ratio depends on plissee size. The firm supportive layer of the plissee is then removed, leaving a single layered gauze with 196 separated graft squares.

[figure not shown]

Meek surgery - <https://ozmedix.com.au/humeca/meek/>

Finally, all single layered plissees are placed with dermal side onto the wound bed and fixated with staplers. Afterwards all ensured plissees are covered with antibacterial gauzes and topped with dry sterile gauzes and bandages. Donorsite is treated with a foam wound dressing with stays on the wound for 14 days. First wound inspection will be conducted after at 8 +/- 2 days to assess the take rate of the graft. Hereafter, daily wound dressing changes will be performed. All residual effects will be treated according to the local standard of care.

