## Follow-up

### Measurements 3 and 12 months after operation

- Regular check-up after hospital discharge
- Preference skin grafting technique
  - Question preference of patient regarding skin grafting technique on this moment
- Scar quality:
  - Patient and Observer Scar Assessment Scale
  - Scar color and pigmentation measurement with Mexameter or Dermaspectrometer
  - Scar elasticity measurement with Cutometer
- Mobility
  - Questionnaire - Quick Disabilities of the Arm, Shoulder and Hand (Quick DASH) - for (burn)wounds concerning upper extremity
  - Questionnaire - Lower Extremity Functional Scale (LEFS) - for (burn)wounds concerning lower extremity
  - Objective measurement of range of motion with a goniometer
- Quality of life
  - Questionnaire - EQ5D-5L
  - Questionnaire - Short Form Health Survey 36-item (SF36)
  - Questionnaire - Dermatology Life Quality Index (DLQI)

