### **10.2 Secondary study parameter(s)**

All continuous data will be assessed with a paired student's t-test, or when data are not normally distributed with a Wilcoxon signed-rank test.

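### Section 10.2 sends time to complete wound closure to a paired t-test or signed-rank test without a rule for wounds that are re-grafted or not seen to close; if their pairs are dropped, a real difference shrinks toward zero

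*Protocol*

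**What the plan says.** Protocol 8.1.2, under healing time, has two items. The first is a percentage healed at fixed days: "Clinical assessment of wound healing 14 and 21 days +/- 2 post application expressed as percentage of the total wound surface area healed". The second is a duration: "Time to complete wound closure where complete wound closure is defined as > 95% re-epithelialization of the wound". The definition also requires no drainage and no further need for a substantial dressing.

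Protocol 10.2 is a single rule: "All continuous data will be assessed with a paired student's t-test, or when data are not normally distributed with a Wilcoxon signed-rank test". Section 10 names no time-to-event method. It does not say how to count a wound with no closure date.

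Four other statements bear on whether a closure date will exist for each wound:

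- 8.1.2 counts as an endpoint "Re-interventions in study areas due to insufficient take or necessity of reconstructive surgery".
- 8.3, under micrografting, says after the first wound inspection at day 8 +/- 2: "Hereafter, daily wound dressing changes will be performed". It gives no end date and no instruction to record closure.
- 8.3, under the heading "Measurements 3 and 12 months after operation", lists grafting preference, scar quality, mobility and quality of life. Wound closure is not on the list.
- Section 3: "Individual patient follow-up is 12 months". Section 8.5 rules out replacement of withdrawn subjects.

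**The concern.** A time in days is continuous data on any ordinary reading, so 10.2 covers it. A paired t-test needs a number for both wounds of a patient. A wound still open when observation ends gives only a lower bound. A wound re-grafted for poor take never shows when the original graft would have closed.

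These are the slow wounds. If software or analyst treats their times as missing, the pair drops out, and the patients removed are those in whom the two techniques may differ most. A real difference is then understated, in favour of the slower technique. Wound healing and epithelisation are named secondary objectives in section 2.

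**Working it through.** **The plan's own figure.** Section 4.4 powers the trial on POSAS, not on closure time. The SD of a paired difference is 2.4 × √(2 × (1 − 0.5)) = 2.4. With 63 pairs the noncentrality is (1 / 2.4) × √63 = 3.31, and two-sided power at 5% is 0.902; 48 pairs give 0.807; 63 / 0.9 = 70. All agree with the protocol. It gives no figure for closure time, so the inputs below are assumptions, apart from the 63 pairs.

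**Assumptions.** Log-normal closure times, medians 20 days (slower) and 17 days (faster), log-SD 0.35, within-patient correlation 0.5, 63 pairs, closure seen only up to day C.

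- True mean difference: (20 − 17) × exp(0.35² / 2) = 3 × 1.063 = 3.2 days.
- Share open at day C: 1 − Φ(ln(C / median) / 0.35). At day 28 this is 1 − Φ(0.961) = 17% for the slower technique and 1 − Φ(1.426) = 8% for the faster.
- A pair is dropped if either wound is open. That share and the power come from 4,000 simulated trials per row.

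| Closure seen to | Open, slower / faster | Pairs dropped | Mean difference in remaining pairs | Signed-rank power, pairs dropped | Signed-rank power, open wounds kept at day C |
|---|---|---|---|---|---|
| Day 23 | 34% / 19% | 42% | 1.7 days | about 60% | about 91% |
| Day 28 | 17% / 8% | 21% | 2.2 days | about 80% | about 93% |
| Day 35 | 5% / 2% | 7% | 2.7 days | about 90% | about 94% |
| Day 60 | 0.1% / 0.0% | 0.1% | 3.2 days | about 93% | about 93% |

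With every time known, power is about 93%. The paired t-test on the remaining pairs gives nearly the same loss.

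**Sensitivity.** With log-SD 0.5 and day 28, 32% of pairs drop and power falls from about 66% to 40%; keeping open wounds restores about 65%. At day 60, 1.9% drop. With medians 18 and 21.6 days (ratio 1.2) and log-SD 0.35, day 28 drops 27% of pairs, the mean difference falls from 3.85 to 2.4 days, and t-test power falls from 0.97 to 0.86.

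**No true difference.** With equal medians of 18 days, dropping 48% of pairs (day 21) or 17% (day 28) leaves the mean difference near 0 and type I error near 5%.

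**Which alternative.** A Cox model stratified by patient has two wounds per stratum and so uses only which closed first. Under the base assumptions the slower wound closes second with probability Φ(ln(20 / 17) / 0.35) = Φ(0.464) = 0.68. A sign test on 63 such pairs has power of about 81% even with complete data, against 93% for the signed-rank test. If a re-grafted wound is censored at re-grafting, before its partner closes, only the partner is at risk when it closes. The stratum then contributes nothing, exactly as if the pair had been deleted.

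**The case against.** A reader might infer that the plan discards these pairs. The documents do not support that: no section excludes them, and a statistical analysis plan, not shown here, could set a counting rule. A reader might also infer that neither named test can cope. For the signed-rank test this is too strong: with unclosed wounds kept at the last observation day it recovers the power, as the table shows. The loss therefore comes from the missing counting rule more than from the choice of a rank test. Both points stand.

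It is also tempting to assume that observation of closure ends soon after "Clinical assessment of wound healing 14 and 21 days +/- 2 post application", because the next scheduled visit is at 3 months. The protocol does not limit dressing changes to inpatients. Its closure definition turns partly on no longer needing a substantial dressing, which dressing care would reveal, and 8.1.2 times some quality-of-life assessments from wound healing, which presupposes a known healing date. If closure is tracked to day 60 or beyond, almost nothing is lost. This also stands, and it is why the day-23 and day-28 rows are illustrations, not forecasts.

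What remains: the protocol fixes a test rule that includes a t-test on a duration, counts re-intervention for poor take as an endpoint, and does not say who dates closure or until when. The simulation contains no re-grafting, so that part is unquantified and does not disappear with longer observation.

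**Conclusion.** The point holds in a conditional form. Section 10.2 as written covers closure time; its t-test cannot use a wound without a closure time, and its signed-rank test can only under a rule that the protocol does not give. If the affected pairs are dropped, a real difference is biased toward zero and power falls: from about 93% to 80% with closure seen to day 28, to about 90% with day 35, and essentially not at all by day 60. These figures rest on assumed medians, spread and correlation and on an assumed end of observation.

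The bias needs both a true difference and a material share of unclosed wounds. A false positive is not made more likely. A patient lost before either wound closes does not show which technique is slower, so that loss does not by itself favour either. This is one secondary endpoint; the POSAS comparison and the 70 patients are untouched. The change is worth making because it is cheap and because a rule set before the data are seen avoids a post hoc choice.

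**What to change.** In Protocol 10.2:

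- Take time to complete wound closure out of the t-test rule. Analyse it with a paired rank test that keeps every pair: a signed-rank test in which unclosed wounds rank as longest (given one common end-of-observation day), or a paired Prentice-Wilcoxon test.
- Count a re-grafted area as not closed to the end of observation, so that it ranks longest. Do not censor it at the re-grafting date.
- Report alongside it the paired proportion of wounds closed at day 21, which comes from an assessment already planned.
- Do not make a patient-stratified Cox model the main test, since it uses only the order of closure within the patient.

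A pair in which neither wound closes is a tie and carries no direction.

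The cost is one or two sentences of analysis text, with no new visits, data or change in treatment. The price is that the mean difference in days is no longer the main summary.

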The second, also currently used method for skin graft expansion is the micrografting technique. It was mainly the need for more manageable and larger expansion ratios in order to increase the survival rate in extensively burned patients that has led to the development of the more labour- and material intensive micrografting technique. With this method, a much more effective expansion of the skin grafts can be achieved, more equal to the claimed expansion ratios resulting in a smaller donor site area. The micrografting technique has been established in many (usually more specialized) burn centers throughout the world due to the easier handling and the lower fragility compared to the widely meshed skin grafts which can be of particular benefit for very extensive burns. For all these reasons, in most burn centers, the micrografting technique is only recommended and reserved for severe burns with at least more than 30-40 % total burned surface area (TBSA).

In addition, and independent of the expansion method, it is important to mention that donor site morbidity actually is an often seriously underestimated problem which in the short term frequently causes the patient more pain than the actual burn.

Since many years, the meshed skin graft technique and the micrografting technique are routinely used (combined) both in Belgium and The Netherlands, therefore providing a true reflection of the current clinical practice. In our burn center extensively (>30%) burned patients are (mostly) treated with the micrografting technique in order to save as much donor site area as possible. During follow-up of many of these patients we often noted a surprisingly good quality of the residual scars following the application of micrografts.

The increased interest in obtaining a good functional and aesthetic outcome after burn surgery is an illustration of the current paradigm shift in burn management from a focus solely on survival towards the overall quality of survival which is often related to the residual scars of the burn patients.

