With this in mind and due to the good results obtained in extensively burned patients we started about 6 years ago to use the micrografting technique in much smaller burns. Our clinical experience showed that the initial graft take as well as scar quality were excellent and donorsite morbidity was substantially reduced. These results together with fact that scar quality of meshed graft technique and micrografting technique has never been prospectively to each other, prompted us to compare this within an adequately developed study.

This study involves a large (intra-individual) randomized controlled trial in a multicenter setting to evaluate the effect of two skin grafting techniques both on the quality of scar formation and the reduction of donor site morbidity. This study is crucial in order to provide evidence for a more widespread use of the micrografting technique and this not only for extensively burned patients but also for smaller burns in need of skin graft expansion. All relevant outcome parameters will be evaluated during acute phase and the follow-up period of 12 months.

Our hypothesis is that treatment with micrografting, when compared to conventional meshed skin grafting, will result in a better scar quality and smaller donorsite size.

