### Secondary Objectives:

- To assess donorsite morbidity, wound healing, epithelisation, mobility and quality of life after skin grafting with micrografting versus mesh grafting.

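### Donor-site morbidity is a secondary objective, but section 8.1.2 measures the donor site only by size and rates pain only in the grafted wounds, so the trial can conclude on donor-site area but not on donor-site morbidity

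*Protocol*

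**What the plan says.** Section 2 (Secondary Objectives) puts donor-site morbidity first: "To assess donorsite morbidity, wound healing, epithelisation, mobility and quality of life after skin grafting with micrografting versus mesh grafting". Section 1 describes the trial as evaluating the effect of the two techniques "both on the quality of scar formation and the reduction of donor site morbidity". It reports from the investigators' experience with smaller burns that "donorsite morbidity was substantially reduced". It also says that donor-site morbidity is underestimated and that it "in the short term frequently causes the patient more pain than the actual burn".

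The Pain item in section 8.1.2 reads "Will be evaluated in the autografted target wounds with help of a Visual Analogue Scale (VAS score) on day 2 post surgery". It continues with ratings around removal of the graft dressing and then weekly in hospital. For the later visits it says "After hospital discharge pain will be evaluated again at the 3 and 12 months follow ups", naming no other site. The only donor-site parameter in 8.1.2 is size, with its ratio to actual graft size, measured in cm² by 3D camera.

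Section 9.2.1 lists post-operative pain and impaired donor-site healing among the known adverse events. It says these will not be reported as adverse events and will instead be followed as secondary outcome parameters.

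**The concern.** The objective names morbidity, while the endpoint list supplies an area. The one symptom that the rationale singles out for the donor site, short-term pain, is rated only at the recipient wounds. Section 9.2.1 adds to the gap: donor-site pain and healing leave the adverse event route on the promise that the endpoint list will hold them, and it does not.

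If the protocol is followed exactly, no record exists from which donor-site symptoms could be compared between techniques. The secondary objective would then be answered by area alone, with the step from less area to less morbidity assumed. An analysis plan cannot repair this, because in-hospital ratings that were never taken cannot be recovered after discharge.

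**Working it through.** **1. Does any planned measure carry donor-site morbidity by technique?**

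| Planned measure | Where | Covers donor-site symptoms or healing, by technique? |
|---|---|---|
| Donor-site size and ratio to graft size | 8.1.2 | No: area only |
| VAS pain | 8.1.2 | No: grafted target wounds |
| Take rate, wound healing, time to closure | 8.1.2 | No: defined on the grafts and the wounds they cover |
| POSAS, including its pain item | 8.1.2, 8.3 | No: concerns the scar |
| EQ5D-5L, SF36, DLQI | 8.1.2, 8.3 | No: one score per patient, and each patient receives both techniques |
| Patient's preferred technique | 8.1.2 | Not separately: one overall choice that may reflect scar, pain, donor site or anything else |
| Adverse events | 9.2.1 | No: pain and impaired donor-site healing are excluded |

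No row delivers donor-site morbidity. The follow-up list in section 8.3 adds nothing for the donor site.

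**2. How large is the expected difference in donor area?**

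Inputs: section 6.4 gives an achieved expansion of 1.36x for mesh set at 1:1.5 and 1.80x for mesh set at 1:3, and says micrografting achieves true ratios. Section 5.1 uses 1:2 for 4-10% TBSA and 1:3 for 11-20% TBSA. Donor skin per cm² of wound is 1 / achieved expansion.

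- 1:3 grafts: mesh 1/1.80 = 0.556 cm²; micrografting, assumed a true 3x, 1/3 = 0.333 cm². Reduction = 1 - 0.333/0.556 = 40%.
- 1:2 grafts: the protocol gives no achieved mesh figure. Assuming it lies between 1.36x and 1.80x, and micrografting is a true 2x, the reduction is 1 - 1.80/2 = 10% to 1 - 1.36/2 = 32%.

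These are areas. Nothing in the protocol links donor area to a VAS score, so no pain difference can be derived from them.

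**3. Is the sample size touched?**

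The protocol's own figures reproduce.

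- POSAS: SD of differences = 2.4 × √(2 × (1 - 0.5)) = 2.4. With a difference of 1 and two-sided alpha 0.05, the exact paired t-test gives power 0.902 at 63 pairs (stated 0.902) and 0.807 at 48 (stated 0.807). 63/(1 - 0.10) = 70.
- Donor-site size: log-scale SD = √(ln(1 + 0.09²) + ln(1 + 0.03²)) = 0.0947. Power is 0.960 at 6 pairs for a ratio of 1.20 (stated 0.960) and 0.914 at 13 pairs for 1.10 (stated 0.914). 6/(1 - 0.10) = 6.7, so 7.

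None of these inputs involves pain or donor-site symptoms, so a further secondary parameter leaves them unchanged.

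**The case against.** The strongest reply is that the pain endpoint is correctly labelled. It says where pain is rated, pain is not itself a named objective, and no section promises a statement on total pain. The hypothesis in section 1 concerns donor-site size, and size is both measured and given a sample size calculation. This stands: pain in the grafted wound is a valid endpoint. It does not answer the gap, because section 2 names morbidity, section 1 names its reduction as a purpose, and section 9.2.1 relies on secondary outcomes that 8.1.2 does not contain.

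A reader might infer that the pain comparison leaves out the place where the techniques are expected to differ, or the larger source of pain, and so could point the wrong way. The documents do not support that. The section 1 sentence presents donor-site pain as a problem whichever expansion method is used, says only that it is frequently worse, and compares it with the burn, not with an excised and grafted wound. Section 1 also expects a difference in scar quality at the grafted wound. A reader might likewise take the 40% as the size of a missed pain effect. It is a donor area, for 1:3 grafts only, under an assumed expansion.

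Feasibility is a fair objection. Both grafts come from the same patient, and the protocol does not require donor areas that the patient can tell apart by technique. Some patients may be unable to assign donor pain to one technique. This limits the remedy but does not remove the need to align the objective with what is measured.

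The weekly preference question is not restricted to the grafted wound, but a single overall choice cannot isolate donor-site symptoms.

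**Conclusion.** The point holds as a mismatch between a stated secondary objective and the endpoints meant to serve it. Donor-site morbidity is to be assessed, but only donor-site size is recorded, and section 9.2.1 closes the adverse event route on a promise that 8.1.2 does not keep. The graft-wound pain endpoint is not wrong, and no bias in it is shown.

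The consequence cannot be put as a number on the pain scale. The area reduction that the protocol's figures imply is 40% for 1:3 grafts (11-20% TBSA, assuming a true threefold micrograft expansion) and about 10-32% for 1:2 grafts under the further assumption stated in the working. How much of that becomes less pain or better healing is unknown, which is the reason to measure it if the objective is kept. The issue is confined to a secondary objective; the primary endpoint, its analysis and the 70 patients are unaffected.

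**What to change.** In section 8.1.2 (Pain), add a VAS rating of the donor area for each technique at the in-hospital sessions already planned: day 2 and weekly. The rationale concerns short-term pain, so ratings at 3 and 12 months are not needed for this purpose. Record which donor area served which technique, which the size ratio already requires. Compare techniques by paired difference under section 10.2, separately from pain in the grafted wound, in patients whose donor areas can be told apart, and report how many could not be rated.

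Reconcile section 9.2.1 with 8.1.2: either list a donor-site healing parameter or remove the statement that it is followed as a secondary outcome.

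Where donor areas cannot be distinguished, or if the rating is not adopted, restate the objective in section 2 and the intended conclusion as donor-site size and pain in the grafted wound only.

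The cost is two VAS questions at sessions already held, the matching CRF fields and a short amendment. The downsides are a slightly longer bedside interview and a comparison that may lose patients with adjacent donor areas.
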